#### Predictors of adherence

Information about baseline socio-demographic characteristics and the following possible predictors of adherence were collected using a structured interview; a positive family (parent, sibling or offspring) history of glaucoma, previous use of eye drops, use of other prescribed medication and if this was used at the same time as travoprost, and self-administration of drops or help given by a family member. Co-morbidity was classified using the Charlson Co-morbidity Index [58] from information available in participant medical records.

A cost effectiveness analysis was undertaken to report the additional cost of delivering a BCC intervention in relation to the potential benefits of increased medication adherence. The analysis included costs from the point of randomisation to completion for each participant (pre-randomisation ophthalmic care and initial consultation costs were not included into the cost analysis).

### Rationale for sample size calculations

The absence of an accepted adherence rate with once daily glaucoma medication [7] and limited research to indicate the likely effect of an intervention led to estimates being derived from general medicine. In general medicine, average non-adherence rates of 25% have been reported [62] with interventions achieving an average 35% adherence increase [23]. Reports of glaucoma adherence studies using medication monitors, have had shorter follow-up time and more complicated dosing regimens than the proposed study [63,64]. Therefore, without a comparable study, a 20% increase in adherence was estimated for sample size power calculations with adherence defined as ≥ 80% of expected doses recorded by TDA. Assuming an adherence rate of 60% in the control group and 80% in the intervention group, 81 people in each group provides 80% power to detect a difference using a Chi-Squared test, at a 5% level of significance. Based on an estimated 20% drop-out rate, a target was set of 200 participants.

### Proposed analyses

Descriptive statistics will be used to characterise the demographics of the study population. All analyses will be based on the intention-to-treat principle. Missing data will be imputed using a multivariate normal imputation model after suitable transformations to ensure that the variables are normally distributed. A total of 10 imputed datasets will be created, each analysed separately and the results averaged using Rubin’s equations. The primary analysis will compare the percentage of “adherers” at 8 months post randomisation between intervention and control using chi-squared. Additionally, the combined month 7 and 8 post randomisation adherence score will be analysed using a *t*-test to compare the intervention and control group. A repeated measures analysis-of-variance will be carried out (with time measured in months) to assess for any difference between intervention and control over time.

Secondary analyses will include a sensitivity analysis of the primary analysis by adjusting for any baseline differences and for possible predictive variables (e.g. severity of disease) using logistic regression. SIMS, MPR and IOP change between 8 months and initial visit will be analyzed using a *t*-test to compare the intervention and control group. A reduction in IOP will be correlated with the percentage adherence rate. A correlation between self-reported adherence and the TDA adherence score will be carried out in each arm separately using a Spearman’s correlation coefficient. The self-reported adherence and SIMS scores will be compared both within the control and intervention groups to assess any changes in perceived quality of information given between the baseline, 2 month and end of study visits, as well as between the two groups to compare any differences. No subgroup analyses are planned.

Logistic regression will be used to identify possible adherence predictors. If appropriate, a multivariate model will be constructed to identify independent predictors of adherence.

The difference in total costs and adherence percentage will be calculated incrementally between the intervention and control group to provide the ICER of additional adherence from the intervention. A deterministic sensitivity analysis will be performed on the base case ICER using patient variability in cost and outcome to determine the robustness of the economic analysis. If there is a high degree of uncertainty, the analysis will be bootstrapped.

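### Ten imputations are few for a planned 20% drop-out: a primary p-value near 0.05 would depend noticeably on the random seed (minor; free to improve)

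*Protocol article*

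**What the plan says.** Under Proposed analyses the Protocol article states "All analyses will be based on the intention-to-treat principle", then "Missing data will be imputed using a multivariate normal imputation model after suitable transformations", and then fixes the number: "A total of 10 imputed datasets will be created", with the separate results pooled by Rubin's rules. The primary test follows: "The primary analysis will compare the percentage of “adherers” at 8 months post randomisation between intervention and control using chi-squared".

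Under Rationale for sample size calculations it gives the design: "Assuming an adherence rate of 60% in the control group and 80% in the intervention group", for which "81 people in each group provides 80% power to detect a difference using a Chi-Squared test, at a 5% level of significance". It adds: "Based on an estimated 20% drop-out rate, a target was set of 200 participants".

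So the article itself sets the number of imputations. It gives no rule that ties the number to the amount of missing data.

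**The concern.** Multiple imputation draws random values for the missing outcomes, so the pooled estimate and p-value vary from one run to the next. The size of that variation depends on the fraction of missing information and on the number of imputations, m. Ten has often been justified by efficiency, meaning how little precision is lost compared with infinitely many imputations. Efficiency does not show whether a rerun would give the same p-value.

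At stake is the repeatability of the primary verdict when the data fall close to 0.05. The trial is sized for 80% power, and the article says that the 20-point effect was assumed without a comparable study. A somewhat smaller true effect, and hence a result near the threshold, is therefore realistic. Two analysts who both follow the plan could then report different conclusions from the same data.

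**Working it through.** **Inputs.** From the article: m = 10; 60% v 80% adherent; 81 per group; 80% power; 5% level (taken as two-sided, since sidedness is not stated); 20% drop-out; 200 participants. Assumed: drop-out means a missing month-8 outcome and nothing else informs it, so the fraction of missing information (FMI) is about 0.20. A range of 0.05 to 0.30 is shown below.

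**The plan's own figure.** With pooled variance and no continuity correction, n per group = [1.96·√(2·0.7·0.3) + 0.842·√(0.6·0.4 + 0.8·0.2)]² / 0.2² = 81.2, so 82; power at 81 is 0.799. Inflation gives 81/0.8 = 101.25, so 102 per group (204 in all), or 81·1.2 = 97.2, so 98 per group (196 in all). The stated 81 and 200 are reproduced closely enough. With 100 per arm and 20% lost, 80 per arm are observed.

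**Efficiency.** Relative efficiency = 1/(1 + FMI/m) = 1/(1 + 0.20/10) = 0.98. Ten is adequate on this criterion.

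**Monte Carlo error of the estimate.** As a share of its standard error it is about √(FMI/m). At FMI 0.20: √(0.20/10) = 0.14; m = 20 gives 0.10; m = 50 gives 0.063; m = 100 gives 0.045.

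**Effect on p at z = 1.96, m = 10.** The 5th to 95th percentile range of z is 1.96 ± 1.645·√(FMI/10):

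| FMI | Range of p over seeds |
|---|---|
| 0.05 | 0.038-0.065 |
| 0.10 | 0.034-0.073 |
| 0.20 | 0.028-0.084 |
| 0.30 | 0.025-0.094 |

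This formula leaves out the noise in the between-imputation variance, which is itself estimated from only 10 draws. In simulation the SD of the pooled t near p = 0.05 is about 0.17-0.18.

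**Simulation on fixed data.** 80 observed and 20 missing per arm, proper beta-binomial imputation within arm, Rubin pooling of the risk difference, 20,000 reruns. For 48/80 v 60/80 observed adherers (complete-case p = 0.043):

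| m | 5th-95th percentile of p | Two reruns disagree at 0.05 |
|---|---|---|
| 10 | 0.021-0.082 | 47% |
| 20 | 0.025-0.066 | 39% |
| 50 | 0.030-0.055 | 23% |
| 100 | 0.033-0.050 | 10% |

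The last column depends on the degrees of freedom and prior used: repeat runs gave up to 17% at m = 100. At m = 10 they gave 47-48%, with p from about 0.02 to 0.085.

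Other data at m = 10:
- 48/80 v 61/80 (complete-case p = 0.027): two reruns disagree in 16%.
- 48/80 v 59/80 (p = 0.065): 38%.
- 48/80 v 64/80, the assumed effect: p about 0.002-0.015, essentially no flips.

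**Simulation over all trials.** Two runs on the same data disagree at 0.05:

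| True rates | m = 10 | m = 50 | m = 100 |
|---|---|---|---|
| 60% v 80% | 5.5% | 2.4% | 1.6% |
| 60% v 75% | 7.8% | 3.3% | 2.3% |
| 60% v 70% | 6.5% | 2.9% | 1.9% |

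A separate simulation at 60% v 80% gave 4.7% at m = 10 and 1.3% at m = 100.

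**Operating characteristics.** With 60% in both arms the rejection rate is 5.3% at m = 10 and 5.2% at m = 100. Power at 60% v 80% is 79.4% and 80.1%.

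**Size of m needed.** For a Monte Carlo error of share c, m = FMI/c². At FMI 0.20: 0.20/0.07² = 41 and 0.20/0.05² = 80. At FMI 0.10: 0.10/0.07² = 20 and 0.10/0.05² = 40.

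**The case against.** The strongest reply is that nothing here is invalid. Inference with 10 imputations is unbiased, holds its level, loses almost no power and has 98% relative efficiency. No finite number of imputations removes seed dependence. All of that stands, and it is why the point is minor.

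The second reply is that an FMI of 0.20 treats drop-outs as uninformative. The article computes adherence for eight monthly periods and follows participants whatever happens to their treatment, and a multivariate normal model can borrow from the observed months. This also stands: 0.20 is towards the upper end of what is likely, and at 0.05 or 0.10 the range of p is narrower, though it still spans 0.05. The simulations also impute a simple binary outcome and use a Wald test, not the planned model and chi-squared, so the percentages are approximate.

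Four stronger readings are tempting and are not supported:
- A reader might infer that about a fifth of runs reach the wrong verdict. In simulation 22% of 10-imputation runs did so, but only among trials whose stable p lies in 0.02-0.10. Over all trials at the design rates, two runs disagree in about 5%.
- A reader might put the noise at a fifth of a standard error. An SD of about 0.21 for the pooled t is an average over trials at the design effect, where t is larger. Near the threshold the SD is 0.17-0.18, and the error of the estimate itself is 0.14 of its standard error.
- A reader might extend the point to every analysis that uses the imputed data. Only the primary comparison was examined, and some analyses, such as the correlations and the cost-effectiveness ratio, have no stated significance verdict to flip.
- A reader might count the absence of a recorded seed or a Monte Carlo check as an omission. Those details may sit in an analysis plan that is not shown. What stands is the low number that the article does fix.

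**Conclusion.** The point holds as a minor matter of reproducibility. With FMI near 0.20, fixing m at 10 leaves enough random noise that near-threshold data can fall on either side of 0.05 by choice of seed. Raising m to 50 or 100 would remove about 3 to 4 percentage points of disagreement between runs at the design rates.

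The conclusion rests on three assumptions: the planned drop-out translates into missing month-8 outcomes, little auxiliary information is recovered, and the simplified imputation and test are a fair guide to the planned ones. If the monthly device data predict month 8 well, the effect is smaller. A clear result, such as one at the assumed 20-point difference, would not be affected.

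**What to change.** Under Proposed analyses, replace the 10 imputed datasets with a larger pre-specified number: at least 50, for example 100. Choose it so that the Monte Carlo error of the pooled primary estimate is below about 5-7% of its standard error. At FMI 0.20, 50 imputations give 6.3% and 100 give 4.5%, so 50 meets the looser end of that range and 100 meets all of it. The change is one sentence of wording and some extra computing time; the design, the data collected and the choice of test stay as they are.

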#### Setting, recruitment and treatment allocation

The study was conducted in the Glaucoma Clinic at the Norfolk and Norwich University Hospital, UK. Patients newly diagnosed, or previously untreated, with either glaucoma or ocular hypertension requiring the standard first line treatment of monotherapy with travoprost, (using established standard criteria as documented in the European Glaucoma Society Guidelines) [52], were invited to participate. Patients were >18 years of age, able to give informed consent, and had adequate ability to read and understand English. Patients requiring care-home staff or home-help (not provided by a co-habiting partner or family member) to apply eye drops were excluded.

Eligible patients were randomised using an automated telephone randomisation system to ensure allocation concealment. Randomisation was stratified by diagnosis (either glaucoma, or ocular hypertension/glaucoma suspect) and experience of the glaucoma service (new patient or follow-up patient but first intention to treat). Stratification controlled for possible variances, since previous studies have shown that patients with suspected glaucoma or ocular hypertension without the presence of manifest glaucomatous disease are less adherent than those with evidence of manifest glaucoma [53,54]. Also, patients previously reviewed as out-patients but not started on ocular hypotensive treatment, had an increased opportunity to ask questions or self-educate before therapy initiation and becoming eligible to participate in the study. Patients declining study participation, following consent, had demographic information collected (age, gender and index of multiple deprivation [IMD]).

Once randomised, participants were followed through to completion of the study regardless of whether travoprost treatment was continued or other additions/changes to the therapy were made.

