**Visit 2**	
Visit 2 Questionnaire (Completed at home)	Satisfaction with Information about Medicines
	Morisky Medication Adherence Score
	Frequency of Missed Dose Score
	Possible predictors of adherence. e.g. do you apply your own drops or does somebody help you?
GSA Evaluation Questionnaire (for intervention group only and completed at home)	Satisfaction with Education and Support from GSAs
Resources log	Time spent with GSA (in minutes)
	Time spent with Clinician (in minutes)
Medical notes	Intraocular pressure measurement

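### Randomisation is stratified on two factors expected to affect adherence, but the planned tests ignore them, and the adjusted sensitivity analysis picks covariates by observed imbalance

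*Protocol article*

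**What the plan says.** Under Setting, recruitment and treatment allocation, the protocol article states: "Randomisation was stratified by diagnosis (either glaucoma, or ocular hypertension/glaucoma suspect) and experience of the glaucoma service". It gives a reason for each factor. Patients without manifest disease "are less adherent than those with evidence of manifest glaucoma", for which it cites earlier studies. Patients already under review but not yet treated "had an increased opportunity to ask questions or self-educate before therapy initiation", which is an argument without a citation. No effect size is given for either factor.

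Under Proposed analyses, the primary comparison is of the percentage of adherers "at 8 months post randomisation between intervention and control using chi-squared". A t-test on the combined month 7 and 8 score and a repeated measures analysis of variance follow. Neither is said to include the stratification factors.

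The only adjusted estimate of the arm effect is a logistic regression, presented as a sensitivity analysis of the primary result, "adjusting for any baseline differences and for possible predictive variables". Its one example is severity of disease. The stratification factors are not named there.

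Table 2 lists, in the questionnaires for visits 2 and 3, items headed "Possible predictors of adherence. e.g. do you apply your own drops or does somebody help you".

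**The concern.** Two matters are involved.

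First, stratified allocation that balances the arms within strata removes between-stratum variation from the difference between arms. An unstratified chi-squared test still counts that variation in its variance. The standard error is then too large, the test rejects less often than its nominal 5%, and some power is lost. The protocol itself says it expects the factors to matter, so it pays for the stratification without using it in the analysis.

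Second, adjusting for whatever differs at baseline makes the model depend on chance. In a randomised trial such differences arise by chance, and an imbalance does not show that a variable is prognostic. The adjusted estimate then depends on which imbalances happened to occur. The other criterion, being possibly predictive, is open-ended and not confined to baseline. An item measured at visit 2 or 3 could have been changed by the intervention, and conditioning on it could remove part of the effect.

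**Working it through.** **Inputs from the protocol article.** Two binary factors, so four strata. Control 60%, intervention 80%, 81 per group, 80% power, 5% level, chi-squared test, 20% drop-out, target 200 (Rationale for sample size calculations). A target of 200 less 20% leaves 160, or 80 per arm.

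**The plan's own figure.** The two-proportion formula (two-sided 5%, no continuity correction) gives 82 per group, and 79.9% power at 81. Inflating for drop-out, 162 / 0.8 = 202.5, so 203 against the stated 200. The figures reproduce to within rounding, and they are for the unadjusted test.

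**Assumptions.** Four equal strata, arms exactly balanced within each, the same odds ratio (OR) for both factors, and marginal rates held at the plan's 60% and 80%. The ORs are assumed, because the documents give none.

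**True size of the unadjusted test.** With both arms at the control rates, the chi-squared variance uses p(1 − p) = 0.6 × 0.4 = 0.240. The actual variance under balanced strata uses W, the mean of p_k(1 − p_k) over strata. With r = W / 0.240, the true size is 2 × [1 − Φ(1.96 / √r)].

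- OR 2: stratum rates 0.43, 0.61, 0.61, 0.75. W = (0.2451 + 0.2379 + 0.2379 + 0.1875) / 4 = 0.227, r = 0.946, 1.96 / √r = 2.015, size 4.4%.
- OR 3: stratum rates 0.35, 0.61, 0.61, 0.83. W = (0.2275 + 0.2379 + 0.2379 + 0.1411) / 4 = 0.211, r = 0.880, 1.96 / √r = 2.090, size 3.7%.
- OR 5: stratum rates 0.25, 0.63, 0.63, 0.89. W = (0.1875 + 0.2331 + 0.2331 + 0.0979) / 4 = 0.188, r = 0.783, 1.96 / √r = 2.215, size 2.7%.

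**Power, by simulation, 80 per arm**, Pearson chi-squared against Cochran-Mantel-Haenszel (CMH):

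| OR, both factors | Chi-squared size | Chi-squared power | CMH power | Gain (points) |
|---|---|---|---|---|
| 2 | 4.4% | 80.4% | 81.2% | 0.8 |
| 3 | 3.7% | 81.6% | 84.1% | 2.5 |
| 5 | 2.8% | 82.6% | 87.5% | 4.9 |

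A separate simulation at 81 per arm (40,000 trials per setting) agrees: 81.2% v 82.4% at OR 2, 81.6% v 84.4% at OR 3, and 80.0% v 80.0% when neither factor matters. CMH size stayed between about 4.8% and 5.2%.

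**Without balance within strata.** If allocation within strata is unrestricted, the chi-squared size is 4.9% to 5.2%, and the conservatism disappears.

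**The sensitivity analysis.** No arithmetic applies. The rule in Proposed analyses has two routes into the model: an observed baseline difference, or being possibly predictive. The first is fixed by the data after allocation. The second has no time limit, and Table 2 uses nearly the same label for items collected at visits 2 and 3. Against that, the section Predictors of adherence says the predictors come from a structured interview, and Table 2 places that interview at the baseline visit.

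**The case against.** The strongest case against the point is that it is a matter of efficiency only. The chi-squared test is valid, the sample size was computed for exactly that test, and the planned power is reached in every setting above. The stratum odds ratios are assumed. The article does not describe blocking, so balance within strata is an assumption too. All of this stands, and it limits the point to a modest recommendation.

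It can also be said that a covariate list is commonly left to the analysis plan. That is fair, and the missing list is not the complaint. The article does state a selection rule, by observed baseline differences, and it does name a primary test that leaves out its own strata.

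Three stronger readings are tempting but not supported:

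- *The trial is underpowered.* A reader who fixes the within-stratum effect (log odds ratio 1.05) can see chi-squared power fall to about 70% to 72% at odds ratios of 5. That setting lowers the marginal intervention rate to 77.6%, and CMH power falls with it, to about 77% to 79%. The plan's assumption is the marginal 60% against 80%, under which the power holds.
- *The primary result is biased.* Ignoring the strata neither biases the comparison nor inflates false positives. Any risk of bias lies in the secondary sensitivity analysis.
- *Adjustment for post-randomisation variables is planned.* The wording only permits it. The sole example, disease severity, is naturally a baseline variable. The visit 2 and 3 items have an evident use in the separate regression for predictors of adherence. Nor do the documents show that the counselling covers who applies the drops. The fidelity section mentions application technique, Figure 1 is not shown, and controls also receive guidance on administering drops.

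**Conclusion.** The point holds as a modest one. The design and the named tests do not match. With balance within strata and marginal rates of 60% and 80%, the unadjusted test has a true size of about 3.7% to 4.4% and forgoes about 1 to 2.5 points of power for assumed odds ratios of 2 to 3. At odds ratios of 5 the loss is about 5 points, and it is nil if the factors are not prognostic. The primary comparison remains unbiased and the 80% power is kept. In the sensitivity analysis, selecting covariates by observed imbalance is a stated and poor rule. The possible entry of post-randomisation items is a gap in the wording and not a stated intention.

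**What to change.** Make the primary test Cochran-Mantel-Haenszel over the four strata, or a logistic or binomial regression with diagnosis and new or follow-up status as fixed covariates. Regression has a further advantage here: each of the 10 imputed datasets yields an estimate and standard error that combine directly under Rubin's rules. If logistic regression is used, report a marginal risk difference as well, so that the result stays on the scale of the 60% against 80% assumption. Include the same two factors in the models for the month 7 and 8 score and for the repeated monthly measures.

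In the sensitivity analysis, drop selection by observed baseline differences. Name a short list of prognostic covariates in advance, all measured before randomisation (disease severity, for example). State that questionnaire items from visits 2 and 3 do not enter any model that estimates the arm effect.

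The cost is a change of analysis wording. Both stratification factors are known at randomisation, and no further data or patients are needed.
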